### Stoprule

The treatment ceases when the patient is completely symptom-free or the patient and the therapist agree that treatment will not further benefit the patient, although their participation in the study will prolong. If patients decide that they no longer wish to participate in the study they are free to withdraw from the study at any moment.

### Control of intervention integrity

To enhance the integrity of this complex intervention, every week all participating physical therapists will discuss the content of each therapy session with the researcher (CB) without mentioning names or other information which will assure the blinding of the independent researcher (CB). After 6 and 12 weeks, the patients of the intervention group will interviewed about the content of the received treatment sessions to assure that all patients will be treated according to the protocol. If patients are not treated according to the protocol, they will be identified and participation may be discontinued.

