### Measurements

Before randomization, all participants will be assessed during an individual baseline test session. They will complete a battery of questionnaires and tests, determining data on social, demographic, and physical factors, and baseline values for the outcome measures. In addition, subjects will complete the DASH, RAND-36-dutch language version, and passive range of motion tests of the shoulder (PROM). During the initial assessment, MTrPs will be identified, based on compression-produced pain that is recognized by patients as their own shoulder pain. If no MTrPs are detected, the subjects will be excluded from the study. All measurements will be performed by the same independent observer, who is not employed by the physical therapy practice (This is to create optimal blinding of the observer, who is now not able to recognise the subjects). The observer is trained in identifying MTrPs and has several years of clinical experience in MTrP therapy. The observer participated in a former reliability study of MTrP palpation. The baseline measurements will be at T0, the second measurement (T1) will be 6 weeks after the first assessment session, the third (T2) will be 12 weeks after the first assessment session. All measurements [see box 1] will be performed outside the physical therapy practice to assure that the observer will not recognise any of the study participants when they come to the physical therapy practice for their treatment. After this first assessment, the patients will be randomly assigned to one of two groups: the intervention group or the control group. The patients in the control group will stay on the waiting list and will not receive any treatment. They are allowed to use over-the-counter painkillers during this 12-week period. After 6 weeks and 12 weeks, respectively, they will be examined by the same blinded observer. After 12 weeks they will receive the same physical therapy program as the experimental group [see Figure 1]. The initial trial ends after 12 weeks, but 6 months and 12 months after the start of the experimental intervention shoulder function of the subjects will be re-evaluated with the DASH-Dutch language version.

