◦ For the measurement of internal rotation the patient is in a prone position. The shoulder is 90° abduction, and the forearm is in neutral position. This position is defined as the position of 0°. The observer than performs internal rotation until pain limits the range of motion or the extreme of the range is reached. The sensor is placed against the volar side of the forearm. The normal range of motion is 70°

◦ For the measurement of horizontal adduction the patient is in a supine position. The arm is in 90° abduction. This position is defined as the position of 0°. The observer performs adduction, while the arm stays in the vertical plane, until pain limits the range of motion or the extreme of the range is reached. The normal range of motion is 135°

• Finally the total number of treatment sessions will be counted. This is done by an assistant, who is not involved in the study by using the administration-software of the practice [see Table 1].

**Table 1 T1:** Overview of variables

**Variable**	**T0 Baseline**	**T1 After 6 wk**	**T2 After 12 wk**	**Measured by**
***Age****	X			Interview
***Gender****	X			Interview
***Work***	X			Interview
***Dominant side affected***	X			Interview
***Duration of the complaints****	X			Interview
***DASH ***DLV	X	X	X	Questionnaire
Use of ***medication***	X	X	X	Interview
Use of ***other therapy***	X	X	X	Interview
***Work ***%	X	X	X	Interview
***Improvement ***(percentage of perceived improvement)		X	X	Interview
***Number of involved muscles***	X	X	X	Assessment
***No. of treatment sessions***			X	Assessment
***Health status ***for baseline comparison	X			RAND-36 DLV
***Existence and severity of symptoms of depression***	X			Beck Depression Inventory
***Shoulder Passive ROM***	X	X	X	Goniometry
• flexion	X	X	X	
• abduction	X	X	X	
• external rotation	X	X	X	
• internal rotation	X	X	X	
• cross body adduction	X	X	X	

*Age, gender and duration of the complaints seem to be important prognostic variables [53].

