### Statistical analysis

For comparisons of prognostic variables on baseline we will use the Student's t test for continuous variables with normal distribution and the chi-square test for categorical variables or continuous variables with non-normal distribution[52]. For the overall score of the DASH (primary outcome measure) we will use the unpaired t-test for normally distributed data or Mann-Whitney Rank Sum-test for non-normally distributed data to assess the difference between the two groups after the treatments. Regression analyses will be used to include prognostic factors, such as the baseline scores like age, gender and duration of the complaints, in the analyses. All significance levels will be set at p < 0.05. All data will be analysed primarily according to intention-to-treat principle. We will use Sigmastat 3.11 and Systat 12 for windows (Systat Inc. Richmond, California, USA) for the statistical analyses.

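### Intervention patients found to be treated off protocol may be removed from the study, with no counterpart in the control arm, which conflicts with the intention-to-treat analysis

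*Protocol article*

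**What the plan says.** Four sections of the protocol article bear on this.

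- **Control of intervention integrity.** Therapists discuss session content every week. In addition, "After 6 and 12 weeks, the patients of the intervention group will interviewed about the content of the received treatment sessions". The consequence is: "If patients are not treated according to the protocol, they will be identified and participation may be discontinued". The section gives no threshold for how large a departure counts and does not say who decides.
- **Stoprule.** Treatment ends when the patient is symptom-free, or when patient and therapist agree that more would not help, "although their participation in the study will prolong". Patients may also withdraw from the study themselves at any time.
- **Measurements, and Table 1.** For the control arm: "The patients in the control group will stay on the waiting list and will not receive any treatment". The DASH is taken at baseline, 6 weeks (T1) and 12 weeks (T2), and again at 6 and 12 months after the experimental intervention starts. Table 1 also records other therapy and medication at T0, T1 and T2, without a split by arm and with no consequence attached.
- **Statistical analysis.** The DASH is compared by unpaired t-test or Mann-Whitney test "to assess the difference between the two groups after the treatments", and "All data will be analysed primarily according to intention-to-treat principle".

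**The concern.** Intention-to-treat needs every randomised patient to be followed and counted in the assigned arm, whatever treatment was received. A rule that lets the trial end participation because of the treatment received works against this. Here it acts after randomisation, at discretion, and in one arm only. A control patient who obtains therapy elsewhere has this noted and stays in. An intervention patient judged off protocol may be removed.

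Timing decides what is lost. After the 6-week interview, the 12-week DASH is lost, and with it that patient's contribution to the primary comparison. After the 12-week interview, the loss falls mainly on the 6- and 12-month DASH, and so on the recurrence aim. An outcome that was never collected cannot be recovered by an analysis plan, so this is more than a detail that could be left to one.

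**Working it through.** **1. What participation means.** The Stoprule section speaks of treatment ceasing when it means the end of therapy, and of participation when it means being in the study. The sentence on control of intervention integrity, which follows directly, uses the second term. The natural reading is removal from the study. No section says that such patients are still measured or kept in the analysis.

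**2. Is there a counterpart in the control arm?** Control patients have no sessions, so there is no session content to ask about. Their nearest departure from protocol is therapy obtained elsewhere, which Table 1 captures in both arms. The asymmetry therefore lies in the consequence and not in the recording.

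**3. The plan's own sample size (context only).** Inputs from the Sample size section: difference 15, SD 22, α = 0.05 (two-sided assumed), power 90%, dropout 5%, 52 per group. A two-sample t-test needs 47 per arm; 47/0.95 = 49.5, so 50, which is within 2 of the stated 52. After 5% dropout, 52 × 0.95 = 49.4 per arm are evaluable.

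**4. Size of a possible bias.** Let a fraction *f* of the intervention arm be removed, and let their mean DASH be *d* points worse than that of the patients retained. If the whole arm has mean μ, the retained patients have mean μ − *f·d*, so

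bias = *f × d*.

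The documents give neither *f* nor *d*; both are assumed. The type I error below takes a true effect of zero, SD 22, and 49.4(1 − *f*) against 49.4 patients, with SE = 22 × √(1/[49.4(1 − *f*)] + 1/49.4) and a two-sided normal test.

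| *f* | bias at *d* = 5 | bias at *d* = 22 | type I error, *d* = 5 to 22 |
|---|---|---|---|
| 5% | 0.05 × 5 = 0.25 | 0.05 × 22 = 1.1 | 5.0% to 5.7% |
| 10% | 0.10 × 5 = 0.5 | 0.10 × 22 = 2.2 | 5.1% to 7.7% |
| 20% | 0.20 × 5 = 1.0 | 0.20 × 22 = 4.4 | 5.5% to 15.5% |

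With *d* = 0 there is no bias. With *d* negative (removed patients did better) the bias keeps its size and changes sign.

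**5. Effect on power alone.** If removal is unrelated to outcome, power at the 15-point effect is 91.7%, 91.0% and 89.2% for *f* = 5%, 10% and 20%.

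**The case against.** - **The rule is permissive and says nothing about analysis.** It says participation may end, not that data are discarded. Voluntary withdrawal also leaves gaps, and handling missing data belongs to an analysis plan that is not shown. A patient removed after the 6-week interview would still have baseline and, as scheduled, 6-week scores. This stands in part: intention-to-treat is not made impossible. But voluntary withdrawal cannot be prevented, whereas this loss is one the trial would impose on itself.
- **The interview belongs in one arm.** It checks the content of delivered sessions, and controls have none. This stands for the interview, and Table 1 does record other therapy in both arms. It does not justify a one-arm consequence.
- **Off-protocol treatment need not follow response.** A reader might infer that poor responders are the ones removed, because session content depends on earlier results. The Intervention section places that variation inside the treatment protocol. The techniques it names as excluded, thrust techniques and dry needling, are tied to therapist skill. Patients given extra techniques could have done better. This stands: the documents supply no direction for the bias.
- **The numbers may be small.** Weekly discussion of content is meant to keep departures few, and at 5% removed the type I error hardly moves. A reader might also infer a power problem, since 5 removals are 9.6% of 52 against a 5% dropout allowance. But 52 − 5 = 47, the number needed before inflation, and 10% removal on top of 5% dropout still leaves 91.0% power.

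**Conclusion.** The conflict is real and should be resolved before the trial relies on its intention-to-treat statement. The protocol allows discretionary removal from the study, in one arm, on the ground of treatment received, and nowhere keeps those patients in follow-up.

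This is a risk of bias, not a demonstrated bias. With 5% to 10% removed and a gap of 5 to 22 points, it is about 0.25 to 2.2 DASH points, at most 15% of the 15-point planning effect (2.2/15). It can run in either direction and is zero if removal is unrelated to outcome. Only heavy removal combined with a large gap distorts the test seriously. A reader might conclude that the comparison will favour the intervention; the documents do not support that.

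The conclusion rests on three readings: that participation means study participation, as the Stoprule section suggests; that the 12-week DASH is the primary time point, since the initial trial ends then; and that T2 is completed at about the time of the 12-week interview, so that removal at that point costs mainly later follow-up. If discontinued patients were in fact measured and analysed as randomised, the conflict would disappear, but the protocol does not say so.

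**What to change.** Reconcile the sections on Stoprule, Control of intervention integrity and Statistical analysis by replacing the discontinuation sentence with wording such as: *Departures from the treatment protocol are recorded as protocol deviations. The patient remains in follow-up (T1, T2, 6 and 12 months) unless he or she withdraws, and is analysed in the arm assigned. The integrity interviews are used only for a supportive per-protocol analysis.*

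This concerns measurement and analysis only; it takes no position on whether or how an individual's treatment continues.

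The cost is one sentence. No visits are added, because all these assessments are already scheduled. The downside is that the estimate includes patients whose treatment was imperfectly delivered; the supportive per-protocol analysis addresses that question separately.

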### Expectations regarding treatment outcome

At the start of the trial (T0) both the patients and physical therapists will complete a questionnaire regarding the anticipated treatment outcome.

### Setting

The study will be conducted in a physical therapy practice specialized in management of persons with musculoskeletal disorders of the neck, shoulder and arm. After randomisation every patient assigned to the experimental group will be treated by the same physical therapist.

### Objectives

In the current study we will test the following hypothesis (H0).

A physical therapy treatment to inactivate MTrPs within a three months' period is as effective as a "wait and see" approach of patients with chronic shoulder complaints in a three month period.

### Population characteristics

• To identify potential confounding factors, demographic information for all subjects will be collected including age, gender, education, occupation, sports and leisure activities, duration of the complaints, and type of onset, among others.

• The Dutch language version of the RAND-36 item Health Survey will be used for base line characteristics of the study population. The RAND-36, which is almost identical to the MOS SF-36 [42], scores the functional status and quality of life and is widely used for screening health status in medical, social and epidemiological research. The RAND-36 consists of 36 items divided into 8 subscales concerning physical functioning, role limitations due to physical health, role limitations due to emotional problems, energy and fatigue, emotional well-being, social functioning, pain, general health perception and health change. This questionnaire is considered to be a reliable instrument for comparing groups (internal consistency Cronbach's alpha > 0.70). The test-retest stability is sufficient (0.58 – 0.82) and the questionnaire is responsive when scoring after at least 4 weeks. The construct validity was estimated by comparing the RAND-36 with other Health questionnaires (like the Nottingham Health Profile [NHP] and the Groninger Activities Restriction Scale [GARS]. There are significant correlations between the subscales of the RAND-36 and the subscales of the NHP (correlation coefficient 0.42 – 0.69). The correlation coefficient between the subscale physical functioning and the GARS is 0.65. A higher score (maximum is 100 points) defines a more favourable health status.

• The Beck Depression Inventory (BDI) is used to discriminate between patients with major depression and those without or with minor depressive feelings. The BDI is included because depression may be a confounding factor. The BDI is widely accepted and used in clinical and experimental research and its predictive value is rated as good. A BDI-score equally or higher than 21 indicates a major depression (specificity 78.4%) [43].

### Outcomes

The following outcome parameters will be used:

#### Primary

The overall score of the DASH (Disability of Arm Shoulder and Hand) questionnaire – Dutch language version will be used as the primary outcome measure. The DASH is a multidimensional (physical, emotional and social) 30-item self-report measure focussing on physical function pain and other symptoms. At least 27 of the 30 items must be completed for a score to be calculated. The assigned values for all completed responses are simply summed and averaged. This value is then transformed to a score out of 100 by subtracting one and multiplying by 25. The transformation is done to make the score easier to compare to other measures using a 0–100 scale. A higher score indicates greater disability.

$$\text{DASH disability/sympton score}=\frac{\left[(\text{sum of n responses})-1\right]}{\text{n}}\times 25$$

where n is equal to the number of completed responses.

Scoring is on a 5-point Likert scale from no difficulty (0 points) to very difficult (5 points). The range of the total score is from 0 to 100, where 0 means no symptoms (pain, tingling, weakness or stiffness) and no difficulty in performing daily activities, while 100 means extreme, severe symptoms and unable to perform any daily activity. Content and face validity of the DASH were confirmed by a variety of experts of the American Academy of Orthopaedic Surgeons (AAOS), the council of Musculoskeletal Speciality Societies (COMSS) and the institute for Work and Health (Toronto, Ontario, Canada) throughout the development process [44].

Its internal consistency was excellent (Cronbach's alpha = 0.96) during field-testing. The test-retest reliability was excellent (ICC_2.1 _= 0.92 and 0.96) in two studies [45,46] and satisfactory in one study (Pearson 0.98 and kappa 0.67). The minimal detectable Change (MDC) was calculated in a population of 172 patients with several upper limb disorders (Osteoarthritis, Carpal Tunnel syndrome, Rotator Cuff syndrome, Rheumatoid Arthritis and Tennis Elbow) [47]. The Minimal Detectable Change (MDC) varied between 10.70 (at 90% confidence level) and 12.75 (at 95% confidence level). The DASH demonstrated to be a responsive questionnaire.

The inter- and intra-observer reliability is good to excellent (intra-observer reliability Pearson r = 0.96 to 0.98; ICC = 0.91 to 0.96; Inter-observer agreement Cohen's kappa = 0.79).

The construct validity was estimated by comparing the DASH to several other questionnaires. The correlation with other instruments like the SPADI (Shoulder Pain and Disability Index) is good (Pearson's r = 0.82 to 0.88). The DASH questionnaire is one of the best among 16 other questionnaires for shoulder symptoms [48].

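### The DASH scoring text gives two different rules and an item coding that do not produce the stated 0–100 score; absolute scores are at risk, the group comparison hardly at all

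*Protocol article*

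**What the plan says.** All the relevant text is in the protocol article, Outcomes, Primary. The DASH is a "30-item self-report measure focussing on physical function pain and other symptoms", and its overall score is the primary outcome.

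The score is then defined in four ways that ought to agree:

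- **Prose rule.** "The assigned values for all completed responses are simply summed and averaged". Then: "This value is then transformed to a score out of 100 by subtracting one and multiplying by 25".
- **Displayed formula.** The bracket in the numerator holds the sum of the responses minus one. That bracket is divided by n and multiplied by 25, "where n is equal to the number of completed responses".
- **Item coding.** "Scoring is on a 5-point Likert scale from no difficulty (0 points) to very difficult (5 points".
- **Range.** "The range of the total score is from 0 to 100", with 0 meaning no symptoms or difficulty and 100 the most severe state.

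On missing items: "At least 27 of the 30 items must be completed for a score to be calculated". So n lies between 27 and 30. No other section of the article restates or corrects the rule or the coding.

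**The concern.** The prose and the formula place the subtraction of one differently, so they are different rules. The coding does not fit either of them: integers from 0 to 5 are six values, whereas the scale is said to have five points. Subtracting one from a mean and multiplying by 25 maps onto 0 to 100 only if the lowest code is 1 and the highest is 5.

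The DASH total is the outcome tested between the groups (Statistical analysis), the basis of the sample size (Sample size), and the only instrument named for the 6- and 12-month re-evaluation (Measurements). A definition that a programmer cannot carry out as written leaves the level of the score open. The article says the transformation exists to ease comparison with other measures on a 0–100 scale, and an off-scale score defeats that purpose.

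**Working it through.** **Inputs** (all from Outcomes, Primary unless noted): 30 items; at least 27 answered; stated range 0 to 100; minimal detectable change 10.70 (90% confidence) to 12.75 (95% confidence). From Sample size: mean improvement 15 points, SD 22.

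**Rules**, with S the sum of the n completed responses:

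- Prose: (S/n − 1) × 25
- Formula: ((S − 1)/n) × 25

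**Step 1: reproduce the stated range.** With items coded 1 to 5, the prose rule gives (1 − 1) × 25 = 0 and (5 − 1) × 25 = 100, for any n. The stated range is reproduced, but with a coding that the article does not state.

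**Step 2: use the coding as stated, 0 to 5.**

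- Prose: (0 − 1) × 25 = −25 and (5 − 1) × 25 = 100.
- Formula, n = 30: (0 − 1)/30 × 25 = −0.83 and (150 − 1)/30 × 25 = 124.17.
- Formula, n = 27: (0 − 1)/27 × 25 = −0.93 and (135 − 1)/27 × 25 = 124.07.

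Neither rule gives 0 to 100.

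**Step 3: try the plausible codings under both rules (n = 30).**

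| Item coding | Prose rule | Displayed formula |
|---|---|---|
| 0 to 5 (as stated) | −25 to 100 | −0.83 to 124.17 |
| 1 to 5 | 0 to 100 | 24.17 to 124.17 |
| 0 to 4 | −25 to 75 | −0.83 to 99.17 |

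Only one of the six cells is exactly 0 to 100.

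**Step 4: size of the formula error.** For the same responses, formula minus prose is 25 × (1 − 1/n):

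- n = 30: 25 × 29/30 = 24.17
- n = 27: 25 × 26/27 = 24.07

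The shift does not depend on the responses, and across the permitted n it varies by only 0.09 points. For scale, moving one item by one category changes the score by 25/30 = 0.83 points. With 1 to 5 coding and the formula used throughout, a patient with no symptoms scores about 24 instead of 0, but the shift cancels, to within 0.09, in any change score or difference between groups.

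**Step 5: size of the coding error.** If items really took values from 0 to 5, the span under either rule would be 5 × 25 = 125 points, so the score is stretched by up to 125/100 = 1.25. As an illustration, assume five response options spread evenly from 0 to 5, so that the stretch is exactly 1.25. The planning effect would then correspond to 15 × 1.25 = 18.75 points and the SD to 22 × 1.25 = 27.5. Their ratio is unchanged (18.75/27.5 = 15/22 = 0.68), but the quoted 15 points, SD 22 and minimal detectable change could not be applied to such scores directly.

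**Step 6: mixing the rules.** If one visit were scored by the prose and another by the formula, change scores between them would carry an artificial shift of about 24 points. That is more than the 15-point planning effect and more than the larger minimal detectable change, 12.75.

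**The case against.** The strongest reply is that the intended score can be recovered from the same section. The prose rule, the five-point scale, the 0–100 range and the two anchors together leave only one reading: items 1 to 5, mean minus one, times 25. The DASH is an existing, validated questionnaire, so a scorer would have to disregard most of the section to go wrong. The position of a minus one relative to a fraction bar is also the kind of detail that can be lost in typesetting or text conversion. Much of this stands, and a reporting slip is a fair description. It does not dispose of the point: the coding sentence is ordinary prose, so conversion cannot explain it, and the prose rule with that coding already gives −25 for a patient without symptoms.

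A reader might infer more: that the primary comparison would be invalid, that the 15-point effect and the minimal detectable change could no longer be used, or that the sample size is affected. The article does not support this. The planned unpaired t-test and Mann-Whitney test are unaffected by a common shift or a common linear rescaling. The 15 points are an improvement and the minimal detectable change is a change, so a constant shift leaves both comparisons intact. The sample size does not depend on the scoring text. The factor of 1.25 is an upper bound that requires items actually to take both 0 and 5, and nothing in the article indicates that a six-level version would be used or that the two rules would be mixed.

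**Conclusion.** The point holds as an internal inconsistency in the definition of the sole primary outcome. Prose and formula are different rules, and neither gives the stated range with the stated coding.

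The consequence depends on what is actually done:

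- **Prose rule, 1 to 5 coding:** no error.
- **Printed formula throughout, 1 to 5 coding:** every absolute score is 24.07 to 24.17 points too high. The anchors at 0 and 100 are lost, and absolute scores cannot be set beside other DASH data on a 0–100 scale. Group differences, change scores and the planned tests are essentially unchanged.
- **Literal 0 to 5 coding, or rules mixed across visits:** comparisons with the 15-point effect and the minimal detectable change would also be disturbed, by a stretch of up to 1.25 or an artificial shift of about 24 points respectively.

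The article does not show which of these would occur. The arithmetic assumes only 27 to 30 completed items and the two rules as printed. It would be going too far to say that the treatment comparison is biased or the trial underpowered for this reason. What can be said is that the outcome cannot be computed as written.

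**What to change.** Make three small changes in Outcomes, Primary and in the scoring program:

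1. Replace the displayed formula by DASH = [(sum of n responses / n) − 1] × 25, with n the number of completed responses.
2. State the item coding as 1 (no difficulty) to 5 (unable, or extreme symptoms).
3. Add a check to the scoring program that all items at 1 give 0 and all items at 5 give 100, at n = 30 and at n = 27. Score every visit, including the 6- and 12-month re-evaluations, with that one program.

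The cost is one formula, one sentence and a short program test. Data collection, sample size and the planned tests do not change.
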